## Abstract

**Introduction:**

Infancy and early childhood are the key stage for the rapid development of brain structure and function, and brain development at this stage has a profound impact on the future intelligence, behavior and health of individuals. A growing body of research suggests that maternal inflammation, as a potential environmental factor, may affect brain development in infants and young children through a variety of mechanisms. Therefore, it is of great significance to evaluate the risk of maternal inflammation to early brain development in infants and young children based on multi-source data modeling to understand the mechanism of early development and prevent brain development disorders.

**Methods and analysis:**

Between December 2021 and May 2024, 360 pairs of pregnant women and their offspring were recruited into the Xiamen Children's Brain Development Cohort. Pregnant women's exposure during pregnancy was collected through standardized and structured questionnaires and medical records. All children were followed up to 3 years of age. We administered questionnaires, behavioral assessments, and performed neuroimaging. Environmental exposures during infancy and early childhood were collected. Children's cognitive, emotional, and linguistic development was evaluated, and blood samples were obtained for whole-exome sequencing and exposure-related biomarker analysis.

**Conclusion:**

In this study, we used deep learning artificial intelligence to construct an early risk assessment model for infant brain development based on the developmental trajectory and developmental results of early brain structure, function, and connections under the complex interaction of “gene-image-environment-behavior” multi-factors, which can improve the early identification and precise intervention of problems in this period, and improve infants cognitive learning and work performance in childhood, adolescence and even adulthood.

**Clinical trial registration:**

https://www.clinicaltrials.gov/; identifier [NCT05040542].

## Introduction

Brain development is currently the most concerned—about frontier field of brain and cognitive science in the world. Brain development during the fetal period is very sensitive to environmental influences. Transcriptional programs in the fetal brain regulate complex developmental processes that ultimately shape the functional structure of the adult brain. Thus, alterations in the intrauterine environment can have far-reaching and long-lasting effects on neurodevelopment (1, 2). Epidemiological data suggest that severe maternal infection during pregnancy is associated with an increased risk of neurodevelopmental and neuropsychiatric disorders, including schizophrenia, bipolar disorder, attention deficit hyperactivity disorder (ADHD), developmental delay, cognitive dysfunction, anxiety/depression, and autism spectrum disorder (ASD), among others (3, 4). In addition, infants experience dramatic changes in brain structure, function, and connections from birth. Synapses are produced in large numbers on the microstructure, and pruning and apoptosis related to the environment and experiences are produced (5); At the macroscopic level, the appearance of magnetic resonance is greatly changed due to the rapid development of axonal myelination. The cortex is significantly thickened, dilated, and folded, and the functional integration is significantly enhanced (6). Long-term follow-up studies have revealed that the cognitive levels reached in infancy and early childhood continue to affect many aspects of physical and mental health, wealth, and longevity in the middle and late adulthood (7). However, currently, our understanding of the mechanisms of these complex brain development processes and the deleterious effects of maternal inflammation on brain development in infants and young children is still limited. Although the micro research carried out in the field of basic neuroscience has reached preliminary conclusions, in order to evaluate the risk factors of brain development and predict the outcome of brain development, it is still necessary to study the brain mechanism of development, especially the map of brain dynamic development, at the macro level. Magnetic Resonance Imaging (MRI), characterized by its non-ionizing radiation and excellent spatial resolution for cerebral tissue, enables the acquisition of multi-parametric information. Furthermore, advanced sequences facilitate functional and biochemical metabolic analyses, thereby providing objective biomarkers for evaluating neonatal brain development and diagnosing cerebral injuries (8). Electroencephalogram (EEG), especially the event-related potential (ERP) technique, can be used to non-invasively explore the cognitive processes of infant speech recognition, language comprehension, phonological awareness, recognition memory, and facial emotion recognition (9, 10). Researchers can, through experimental paradigms specifically designed for different age groups, explore ERP components, characteristics, origins, and influencing factors of language and social-emotional development in infants and toddlers aged 0–3 years (11). These imaging techniques, combined with brain image modeling, can reveal the mysteries of early brain development and the impact of maternal inflammation. Due to the limitations of technology and research objects, it is very difficult to study infant brain development. Under the promotion of the Human Connectome Project (HCP) in the United States, the leading Infant Connectome Project (BCP) has been successfully carried out (12), which has led to a boom in research on infant brain development. Since the 13th Five-Year Plan, China has been taking brain science as a national strategy. Artificial intelligence has been regarded as “a strategic technology to lead this round of scientific and technological revolution and industrial transformation”.

Deep learning technology has made a very important breakthrough in the field of artificial intelligence in the past decade. The availability of big data, the enhancement of computer computing power, and the innovation of deep network training algorithms have greatly promoted the great progress of deep learning technology in many fields, including computer vision, natural language processing, speech recognition, medical image analysis, and disease diagnosis (13–15). In clinical studies, a large amount of multimodal neurobiological information such as neuroimaging, electrophysiological and behavioral data is usually collected from patients, which provide important data support for the early risk assessment of brain development and the prediction of brain development trajectory and results. Deep learning provides effective technical support for mining and understanding the differences and mechanisms of brain development. It is of great scientific significance and application value to analyze, based on deep learning technology, multimodal neurobiological data, develop an accurate and efficient early risk assessment model for brain development, and explore neural biomarkers related to brain development. At present, deep learning networks that are widely used in brain development research mainly include deep belief networks (DBN), convolutional autoencoders (CAE), convolutional neural networks (CNN), graph convolutional networks (GCN), and recurrent neural networks (RNN) (16, 17).

Therefore, this study will establish a 0–3-year-old infants' brain development assessment cohort, collect multimodal neurobiological data, including multi-source data of imaging, EEG, behavior, genes, and environment, and use deep learning artificial intelligence methods to construct an early risk assessment model for infant brain development under maternal inflammation, and carry out individualized comprehensive assessment and prediction of brain intelligence. The aim is to accurately identify and distinguish brain development disorders in infants and young children, and to discover the neural mechanism in the brain network based on the proposed interpretable artificial intelligence method, to propose a new method for the clinical assisted diagnosis and assisted rehabilitation of brain development.

## Objectives

Establish a brain development assessment cohort for infants and young children aged 0–3 years, and collect multimodal data of “gene-image-environment-behavior” through high consistency, high success rate, high follow-up rate and high quality.Use MRI and EEG and image recognition technology to depict the early development trajectory of brain structure, function and connection of these high-level functions.Integrate multi-source data: use deep learning artificial intelligence methods to construct an early risk assessment model for infant brain development under maternal inflammation, and conduct individualized comprehensive assessment and prediction of brain intelligence.Integrate whole-exome sequencing and whole-genome sequencing results to identify genes that play a key role in children's early life development. Also, identify how these genes interact with maternal inflammation to affect children's brain structure and function development.

## Methods and analysis

### Research subject

The study subjects were infants and children aged 0–3 years and their mothers, and the Xiamen Children's Brain Development Cohort recruited the study subjects from the society (kindergartens, elementary schools, and other institutions) and the neonatal department of Xiamen Children's Hospital. Based on the information of the mothers' pregnancy—related medical history, infants whose mothers had high inflammatory indices during pregnancy (e.g., CRP, interleukin−1β, interleukin−6, interleukin−10, and macrophage inflammatory factor−1β), or had chorioamnionitis, pathologic abnormalities of the placenta, preterm premature rupture of the membranes, or had combined gestational hypertension and diabetes mellitus with maternal inflammatory diseases were included in the observation group. Infants without maternal inflammation were the control group.

Characteristics of our included subjects included:(1) age 0–3 years;(2) gestational age 37–42 weeks;(3) birth weight >2.5 kg; and(4) no significant birth complications. Characteristics of excluded subjects included:(1) history of resuscitation from asphyxia at birth;(2) congenital structural anomalies;(3) presence of inborn inherited metabolic disorders such as phenylketonuria, galactosemia, and congenital hypothyroidism;(4) presence of a major medical condition affecting growth, or development; and(5) contraindications to magnetic resonance imaging (MRI).

#### Sample size

The formula for calculating the sample size is based on the comparison of the average values of the two independent samples:

$$\begin{array}{l} N\;=\;\frac{{2\left(Z_{\alpha }+Z_{\beta }\right)}^{2}\sigma^{2}}{d^{2}} \end{array}$$

Where σ is the estimated standard deviation, *d* represents the difference between the two sample means, and *Z*_α_ and *Z*_β_ are the quantiles of the standard normal distribution corresponding to α and β, respectively. A previous Greek study using the McCarthy Scales for Children's Abilities to measure children's brain development found that the difference between the memory scores of children born to mothers with a hyperinflammatory state during pregnancy and those born to normal mothers was −4.4 (−8.3, −0.5) (18). Substituting σ = 0.05 and β = 0.2 gives *N* = 1603, based on a 1:1 calculation of mothers in the inflammatory group vs. the normal group, a total of 2*N* = 3206 pregnant women needed to be included in the entire study.

Hospital clinicians and nurses explained the objectives of the study, the process, the potential benefits of participation, and the confidentiality of the study to all families eligible for inclusion. All investigators entering the cohort signed an informed consent form. The Xiamen Child Brain Development Cohort provided each mother and child pair with a unique family ID for further follow-up. Participants could withdraw from the cohort at any time. The study was approved by the Clinical Ethics Committee of Xiamen Children's Hospital and the participating hospitals.

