#### Follow-up plan

Utilizing an aggregation cross design, referencing the grouping methodology of the Baby Connectome Project (BCP) by UNC/UMN in the USA (12), participants were categorized into 9 sub-cohorts based on the age at initial enrollment, each having varying sampling density and age spans (Table 1). Each of the first three sub-cohorts enrolled 536 participants, while sub-cohorts 4–9 each enrolled 268 participants, totaling 3,216 participants. Each participant was followed up 3–4 times, yielding data from 11,256 participant—visits. Moreover, the follow-up intervals for sub-cohorts 1–3 and 4–9 were 3 and 6 months, respectively, ensuring sufficient sampling density during the first year, which is critical for rapid development in language and socio-emotional skills. Oversampling was strategically implemented during milestones of language and socio-emotional development and periods prone to scan failures (before the age of 3). Considering the low cooperation levels of infants and potential dropouts, 3,847 participants were recruited to ensure the acquisition of high-quality data from 3,216 subjects (Figure 1).

**Table 1 T1:** Cohort design and follow-up time planning schedule.

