**Aggregated cross design**						
**Cohort number**	**Number**	**Follow-up**				**Note**
		**First**	**Second**	**Third**	**Fourth**	
1	536	0	3	6	9	High-density sampling: once every 3 months
2	536	1	4	7	10	
3	536	2	5	8	11	
4	268	10	16	22		Medium-density sampling: every 6 months
5	268	6	12	18		
6	268	9	15	21		
7	268	12	18	24		
8	268	15	21	27		
9	268	24	30	36		
Total	3,216	Number of Participant—visits: 11,256			
Target number	3,847	Considering the failure rate of magnetic resonance imaging and the dropout rate of the cohort, the effective enrollment was guaranteed to be >11,256 cases				

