**Behavioral assessments**								
Developmental level	Griffiths Development Scales-Chinese Edition (GDSC) (19)		√	√	√	√	√	
Intelligence	Wechsler Intelligence Scale for Children—Fourth Edition (WPPSI-IV) (20)							√

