#### Behavioral assessment

(1) Griffiths Development Scales—Chinese Edition (GDSC) (57): Griffith assessment was performed during the follow-up of preterm infants after discharge. Griffiths scale is a standardized assessment scale for children aged 0–8 years whose mother tongue is Chinese and which has Chinese norms. The scale is divided into two parts: 0–2 years old and 0–8 years old, the 0–2 years old part is composed of 5 domains: “A Movement”, “B Individual-Society”, “C Language”, “D Hand-eye Coordination” and “E Performance”, and the 0–8 years old part adds “F Practical Reasoning Domain” on this basis. When the developmental quotient DQ < 70, it indicates developmental delay; when DQ ≥85, it indicates normal development.(2) Wechsler assessment: this study uses the WPPSI—IV (58) to assess the child's intelligence level. Five scores are calculated from the questionnaire, namely the Verbal Comprehension Index (VCI), Visual Spatial Index (VSI), Working Memory Index (WMI), Fluid Reasoning Index (FRI), and Processing Speed Index (PSI). Then, the scores of different ability areas will be summarized based on the questionnaire data to obtain the Full Scale IQ (FSIQ) score, which comprehensively reflects the overall intellectual level of children. Different intellectual level intervals are divided according to the FSIQ.

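### The only sample-size justification rests on a memory score the study does not collect, and the nearest measure, the WPPSI-IV, is scheduled for 536 of 3,216 children

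*Protocol article*

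**What the plan says.** The Sample size section uses the two-means formula. Its effect comes from a Greek study "using the McCarthy Scales for Children's Abilities to measure children's brain development found that the difference between the memory scores" of children of hyperinflammatory mothers and "those born to normal mothers was −4.4 (−8.3, −0.5" in brackets. It continues "Substituting σ = 0.05 and β = 0.2 gives" 1,603, and doubles this to 3,206, "based on a 1:1 calculation of mothers in the inflammatory group vs. the normal group".

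The Follow-up plan then divides the cohort: "Each of the first three sub-cohorts enrolled 536 participants, while sub-cohorts 4–9 each enrolled 268 participants, totaling 3,216 participants". Table 1 gives each sub-cohort three or four visits. Sub-cohorts 4–9 carry the note "Medium-density sampling: every 6 months".

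Table 2 lists the instruments by age. The Griffiths scales (GDSC) are ticked in every column from 0–1 to 19–24 months. The Wechsler test (WPPSI-IV) is ticked for 25–36 months only. The Behavioral assessment section lists five GDSC domains for 0–2 years: movement, individual-society, language, hand-eye coordination and performance. Among the WPPSI-IV scores it lists the "Working Memory Index (WMI").

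The secondary outcome on maternal exposure, and the matching paragraph under Data analysis, plan to compare children's intelligence, cognitive and other abilities by inflammatory level. Neither names a memory score.

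**The concern.** A sample size means something only for an outcome that is measured in the children it counts. Here the outcome behind the number is not measured at all, and its closest substitute is scheduled only at ages that most sub-cohorts never reach. A reader who sees 3,206 beside a planned comparison of intelligence by maternal inflammation will assume that about 3,200 children stand behind it. A null WPPSI-IV result could then be given more weight than about one sixth of that number supports.

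**Working it through.** **1. The plan's own figure.** N = 2(Zα + Zβ)²σ²/d², with d = 4.4, β = 0.2 and Zα + Zβ = 1.960 + 0.842 = 2.802 (two-sided alpha 0.05 assumed).

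- With σ = 0.05 as printed: 2 × 7.849 × 0.0025 / 19.36 = 0.002, so 1,603 does not reproduce.
- If 0.05 was meant as alpha, no SD is stated. Then 1,603 implies SD = 4.4 × √(1603 / (2 × 7.849)) = 44.5.

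The count in steps 2 and 3 does not depend on this.

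**2. Which scheduled instrument gives a memory score?**

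- McCarthy Scales: not in Table 2 at any age.
- 0–24 months: none of the five GDSC domains is memory. The questionnaires, observation tasks and EEG tasks (resting, language, emotion) are not described as yielding a memory score.
- 25–36 months: WPPSI-IV working-memory index.

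**3. Which children have a visit at 25–36 months (Table 1)?**

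| Sub-cohort | Children | Last visit (months) | Visits after 24 months |
|---|---|---|---|
| 1, 2, 3 | 536 each | 9, 10, 11 | 0 |
| 4, 5, 6, 7 | 268 each | 22, 18, 21, 24 | 0 |
| 8 | 268 | 27 | 1 |
| 9 | 268 | 36 | 2 (30 and 36) |

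- Children: 268 + 268 = 536; 536 / 3,216 = 16.7%; 268 per group at 1:1.
- Visits: 268 × 1 + 268 × 2 = 804; 804 / 11,256 = 7.1%.
- Closure check: 3 × 536 × 4 + 6 × 268 × 3 = 6,432 + 4,824 = 11,256, the printed total. The schedule holds no further visits for the other 2,680 children.
- Counting the 24-month visit as well would add sub-cohort 7: 804 children, 25% of 3,216.
- The 536 is a share of the 3,216 that recruitment of 3,847 is meant to secure. Spread proportionally, it corresponds to about 641 recruited (536 / 3,216 × 3,847).

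**4. What each size detects** (80% power, two-sided alpha 0.05 assumed): difference in SD units = 2.802 × √(2/n).

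- n = 1,603 per group: 0.099 SD.
- n = 268 per group: 0.242 SD.

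**5. Power for 4.4 points with 268 per group.** Power = Φ(4.4 / (SD × √(2/268)) − 1.960). All SDs are assumptions, since the document gives no usable one.

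| SD | Power |
|---|---|
| 15 | 92% |
| 20 | 72% |
| 30 | 40% |
| 44.5 (implied by N = 1,603) | 21% |

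Power is at least 80% when the SD is about 18.2 or less: 4.4 / 0.242 = 18.2.

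**The case against.** Four objections deserve an answer.

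- **No memory comparison is planned.** This is correct. The McCarthy result serves as an effect-size source, and the primary outcomes are data integrity, brain mapping, model AUC and gene interactions. A reader might infer that a planned memory analysis has become impossible. The document does not support that, because it names no such analysis. What remains is that the single size justification is detached from every stated outcome, while intelligence and cognitive ability are to be compared by inflammatory level.
- **The study may not be underpowered.** Also correct. A reader might take 21% as the power for memory. That figure needs the SD of 44.5, which only follows from an N that does not reproduce; at an SD of 15 the power would be 92%.
- **The Abstract says every child was followed to age three.** If so, all children would reach the WPPSI-IV window. Table 1 contradicts this: only sub-cohort 9 has a 36-month visit, and the visit total matches Table 1 exactly. The two statements must be reconciled.
- **Other outcomes do cover the whole cohort.** They do. GDSC is scheduled at least once in each sub-cohort, but so are MRI, EEG and ASQ:SE-2, so GDSC is one candidate for the size statement and not the only one. Its coverage is itself unclear: the Behavioral assessment section places Griffiths testing in the follow-up of preterm infants, whereas the inclusion criteria require 37–42 weeks.

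A separate analysis plan could settle which scale serves which comparison. It could not supply a score at visits that are not scheduled.

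**Conclusion.** The point holds in this form: 1,603 per group is justified by an outcome that the study neither schedules nor names, and it does not describe the size available for memory or IQ. Under Table 1 that size is 536 children, about 268 per group if the groups split 1:1 and losses stay within the allowance. The detectable difference is then about 0.24 SD, not 0.099 SD. The counts come straight from Tables 1 and 2; the detectable differences assume two-sided alpha 0.05 and 80% power.

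It does not follow that 268 per group is too few, since that depends on an unstated SD. If 268 suffices, this endpoint does not justify 3,206; if 3,206 is needed, the schedule does not deliver it. The stated primary outcomes do not depend on a memory score, so the defect lies in the size statement and in how WPPSI-IV comparisons will be read.

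**What to change.** In the Sample size section:

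1. State that 3,206 is not the number available for memory or IQ. WPPSI-IV comparisons by inflammation group rest on at most 536 children (sub-cohorts 8 and 9), with a detectable difference of about 0.24 SD, and are exploratory.
2. Tie the size statement to an outcome scheduled in all nine sub-cohorts and used in the comparison by inflammatory level, for example the GDSC developmental quotient at 0–24 months. As the document gives no GDSC difference or SD, express it as a detectable standardised difference for the planned 3,216 children: with one score per child and 1,608 per group, 2.802 × √(2/1608) ≈ 0.099 SD.
3. In the same edit, reconcile the Abstract's statement on follow-up with Table 1, and the preterm wording on Griffiths testing with Table 2 and the gestational-age criterion under Research subject.

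The cost is protocol wording and the choice of one outcome. No child, visit or test is added. The downside is a less favourable stated size for memory and IQ.

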## Preliminary results

Between December 2021 and May 2024, 360 pairs of pregnant women and their offspring were recruited into the Xiamen Childhood Brain Development Cohort, which investigated basic family information through a baseline questionnaire, children's births through medical information, and MRI scans of children's brains who entered the cohort. Of the 360 children enrolled in the study (Table 4) , 203 (56.39%) were males, the mean gestational week of the mother's pregnancy was 35.67 weeks, the mean age of the children at MRI was 3.28 weeks, and there were a total of 163 (45.3%) children born at term and 156 (43.3%) children born by normal delivery.

**Table 4 T4:** Baseline characteristics and risk factors of research subjects.

**Variable**	**Sum mean (sd)**	**Male mean (sd)**	**Female mean (sd)**	** *p* **
People (%)	360	203 (56.39)	157 (43.61)	
Gestational age (week)	35.67 (3.88)	35.85 (4.03)	35.45 (3.68)	0.332
Age at scanning (week)	3.28 (3.30)	3.25 (3.49)	3.31 (3.05)	0.849
Full-term infant (%)	163 (45.3)	102 (50.2)	61 (38.9)	0.041
Birth weight (g)	2.49 (0.87)	2.58 (0.87)	2.37 (0.85)	0.024
Vaginal delivery (%)	156 (43.3)	97 (47.8)	59 (37.6)	0.067
Parity (%)				0.141
0	55 (15.3)	30 (14.8)	25 (15.9)	
1	163 (45.3)	84 (41.4)	79 (50.3)	
≥2	142 (39.4)	89 (43.8)	53 (33.8)	
Chorioamnionitis (%)	7 (1.9)	4 (2.0)	3 (1.9)	1.000
Gestational hypertension (%)	40 (11.1)	18 (8.9)	22 (14.0)	0.170
Gestational diabetes (%)	76 (21.1)	38 (18.7)	38 (24.2)	0.257
Pathological placental abnormalities (%)	7 (1.9)	2 (1.0)	5 (3.2)	0.265
Premature rupture of membranes (%)	47 (13.1)	25 (12.3)	22 (14.0)	0.752
Eclampsia (%)	27 (7.5)	13 (6.4)	14 (8.9)	0.486
Sexually transmitted diseases (%)	28 (7.8)	15 (7.4)	13 (8.3)	0.909
Antibiotic treatment (%)	68 (18.9)	34 (16.7)	34 (21.7)	0.297
Maternal inflammatory (%)	187 (51.9)	94 (46.3)	93 (59.2)	0.020

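### N = 1603 per group does not follow from the printed inputs: the symbol defined as the SD is given 0.05, no SD is stated, and the later cohort totals appear to inherit the figure

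*Protocol article*

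**What the plan says.** The Sample size section sizes the study on a comparison of two means: "The formula for calculating the sample size is based on the comparison of the average values of the two independent samples". The formula is N = 2(Zα + Zβ)²σ²/d². The text then defines its symbols. "Where σ is the estimated standard deviation", d is the difference between the two means, and Zα and Zβ "are the quantiles of the standard normal distribution corresponding to α and β, respectively".

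The effect comes from one cited source. "A previous Greek study using the McCarthy Scales" is credited with a difference in memory score of −4.4, with an interval of −8.3 to −0.5. The substitution follows: "Substituting σ = 0.05 and β = 0.2 gives" N = 1603, and with 1:1 groups 2N = 3206. The section gives no numerical α, no sidedness and no other SD.

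The Follow-up plan section and Table 1 then set nine sub-cohorts (three of 536, six of 268) totalling 3,216, with 11,256 participant-visits. The text adds that "3,847 participants were recruited to ensure the acquisition of high-quality data from 3,216 subjects". The Preliminary results section reports that "360 pairs of pregnant women and their offspring were recruited into the Xiamen Childhood Brain Development Cohort" between December 2021 and May 2024, and the Abstract gives the same count.

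**The concern.** In a two-means calculation the SD drives the answer, because N scales with its square. Here the symbol defined as the SD receives 0.05, a value that is a conventional significance level and is paired with β = 0.2. α itself receives nothing. If 0.05 is a misplaced α, correcting the letter does not restore the result, because the SD behind 1603 is then missing altogether.

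At stake is the basis of the planned cohort. Several thousand infants are to have repeated MRI and EEG, and blood is drawn at enrolment, on the strength of this number. A reader cannot tell what difference the study was sized to detect, or with what variability.

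**Working it through.** **Inputs.** From the Sample size section: the formula, d = 4.4 in absolute value, β = 0.2 (so Zβ = 0.842), 1:1 groups, and σ printed as 0.05. Assumed, because not stated: α = 0.05, tried two-sided (Z = 1.960) and one-sided (Z = 1.645). The formula prints Zα, which does not settle the sidedness.

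**1. The plan's own figure, inputs taken literally.** Two-sided, 2(1.960 + 0.842)² = 15.698.

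N = 15.698 × 0.05² / 4.4² = 15.698 × 0.0025 / 19.36 ≈ 0.0020.

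One-sided gives about 0.0016. Putting either end of the interval (8.3 or 0.5) in place of d, with σ still 0.05, also rounds up to 1 per group. 1603 is not reproduced.

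**2. Reading 0.05 as α and solving for the SD that 1603 requires.** σ = d × √(N / 15.698) = 4.4 × √(1603 / 15.698) ≈ 44.5 two-sided. With the one-sided constant the result is about 50.1. The standardised difference is 4.4/44.5 ≈ 0.099, or 4.4/50.1 ≈ 0.088. If 1603 were the total rather than the per-group size, the SD would have to be about 31.4 (two-sided) or 35.4 (one-sided). None of these SDs appears in the article.

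**3. Sensitivity to the missing SD.** With d = 4.4, α = 0.05 and 80% power, all SDs being assumptions:

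| Assumed SD | N per group, two-sided | N per group, one-sided |
|---|---|---|
| 10 | 82 | 64 |
| 15 | 183 | 144 |
| 20 | 325 | 256 |
| 30 | 730 | 575 |

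**4. Sensitivity to d.** The quoted interval runs down to 0.5. At d = 0.5 and an assumed SD of 15, two-sided, N = 15.698 × 225 / 0.25 ≈ 14,128 per group. At d = 0.5, N = 1603 would correspond to an SD of about 5.05, but the article states neither choice.

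**5. Carry-through.**
- 2 × 1603 = 3206.
- 3206 / 12 rounds up to 268, and 12 × 268 = 3216 = 3 × 536 + 6 × 268.
- 1608 × 4 + 1608 × 3 = 11,256 participant-visits.
- 3206 × 1.2 = 3847.2, matching 3,847 (3216 × 1.2 would be 3,859).

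The article does not state these derivations. The fit is close enough to infer that the later totals were built on 1603.

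**6. Endpoint.** Table 2 lists the Griffiths scales and the WPPSI-IV but no McCarthy scale. The four primary outcomes are data integrity, brain development mapping, a risk model with AUC of at least 0.8, and gene-environment interaction. Comparing children by maternal inflammatory level appears under the secondary outcome and its analysis.

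**The case against.** The strongest reply is that this is a misprint in a condensed article: σ stands for α, and the SD sits in a fuller protocol that is not shown. That may be so, and it is why the misplaced α is called an inference here. It does not dispose of the point. The article prints a formula, a set of inputs and a result, and the result does not follow from the inputs. The SD that would rescue it is about ten times the difference sought and would need a stated source.

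Three further replies have some force. First, a comparison of ability scores by inflammatory level is planned, and the WPPSI-IV yields a Working Memory Index, so the sizing comparison is not foreign to the study. It remains secondary and on a different scale. Second, the Follow-up plan credits its grouping method to the Baby Connectome Project, so the link from 1603 to 536 and 268 is arithmetical inference, not a stated derivation. Third, Table 1 labels 3,847 a target, so the past tense in the text is a wording fault separate from the arithmetic.

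A reader might also infer that the cohort is several times too large. The documents do not support that. The SDs of 10 to 30 are assumptions, d could be smaller than 4.4, and this comparison says nothing about what the prediction-model or gene-environment aims need. Nor do they support a power figure for the 360 pairs already recruited. The sizing scale is not collected, and only 163 of those children were born at term although the inclusion criteria require 37 to 42 weeks.

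**Conclusion.** The point stands in this form: N = 1603 is irreproducible as printed, and the article lacks the SD, α and sidedness needed to repair it. Literally, the inputs give about 0.002. With 0.05 read as α, they require an unstated SD of about 44.5 to 50.1. Correcting the symbol alone is therefore not enough. The right N cannot be determined from the article and could move in either direction with the SD and d chosen. That 0.05 is the misplaced α, and that 3,216, 11,256 and 3,847 descend from 1603, are both inferences, though well supported ones. This should be corrected before the stated size is relied on.

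**What to change.** In the Sample size section, correct the symbol and state α, its sidedness, d, and an SD with its source, in the units of an outcome that Table 2 collects. Say that the comparison sized is a secondary outcome. Then either recompute N, or keep 3,206 and state the difference it can detect at 80% power: with 1603 per group this is about 0.099 SD two-sided or 0.088 SD one-sided at α = 0.05.

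Carry the result through 2N, the sub-cohort sizes, the participant-visits and the recruitment target in the Follow-up plan and Table 1, and state how each was obtained. Reword the Follow-up plan so that the sub-cohort counts and 3,847 read as planned targets, distinct from the 360 pairs reported as recruited.

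The cost is a recalculation and edits to two sections and one table. No new data are needed.
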